### Post-operative care

Post-operatively, all in-patient participants will receive multi-disciplinary support as part of rehabilitation including allied health, multi-modal analgesia, and critical care for those hospitalised in the intensive care unit. Participants deemed fit to be discharged from the hospital in between the dressing changes prior to full re-epithelialisation; will be given a standardised patient information card with emergency numbers and basic dressing advice. In addition, participants will be advised to report any concerns regarding the dressing to staff at the study setting especially should fever or erythema develop at home. A schematic representation of the assessment timeline is illustrated in Table 2.

**Table 2 Tab2:**
[figure not shown]
Data collection and assessment timeline for the trial

*COD* change of dressing, *DOI* date of injury, *TBSAB* total body surface area burned, *3D* three-dimensional, *2D* two-dimensional, *FLACC* Face, Legs, Activity, Cry, Consolability, *FPS-R* Faces Pain Scale-Revised, *NRS-P* Numeric Rating Scale–Pain, *NRS-P*
*Proxy* Numeric Rating Scale–Pain Proxy, *NRS-I* Numeric Rating Scale–Itch, *NRS-I*
*Proxy* Numeric Rating Scale–Itch Proxy, *POSAS* Patient and Observer Scar Assessment Scale, *BBSIP* Brisbane Burn Scar Impact Profile, *CHU9D* Child Health Utility 9D, *RES™* Regenerative Epithelial Suspension

### Monitoring

Minimal adverse events are expected from the proposed interventions. At the study centre, known potential adverse events (e.g. infection, haematoma, intensive care admissions) have a standardised management protocol. Adverse events related to the interventions will be monitored through review of patient medical records, by guardian and participant (where applicable) self-report and by the treating clinicians. All adverse events will be communicated to the clinical health service and Human Research Ethics Committee (HREC). Discontinuation or alteration of treatment will be at the discretion of the treating clinical team. An independent Safety Monitoring Group will also monitor all aspects of patient safety throughout the study on a regular basis. An interim analysis will be completed by an independent statistician, who will be blinded to the treatment allocation after a minimum of 30 participants have been recruited.

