Mepilex Ag® is a silver sulfate soft silicone foam dressing that allows for continuous silver delivery to the wound, good exudate management, provides a moist environment and thermal insulation making this dressing ideal for partial thickness burns [25]. In a randomised trial of children (*n* = 96) with partial thickness burns, silver-impregnated foam dressings were effective in shortening the TTRE and reduced pain during dressing changes [9]. Despite this, silver impregnated dressings are more expensive per dressing change when compared to Biobrane® and a Regenerative Epithelial Suspension (RES™) [10], require frequent dressing changes due to non-transparent design and are associate with adverse effects such as cytotoxicity and argyria. Over the last 30 years, epithelial suspension preparation for burn wound management has undergone a multitude of transformations including the number of enzymatic degradation agents used, co-delivery systems with various cell carriers and a range of preparation times (few weeks to under an hour) [7, 26]. The RECELL® Autologous Cell Harvesting (ACH) device (Avita Medical, California, USA) was first introduced almost two decades ago [27]. In approximately 30 min, a Regenerative Epithelial Suspension (RES™) containing basal keratinocytes, melanocytes, fibroblasts, melanocytes, Langerhans cells and epidermal basal cells [28] is obtained from a donor skin sample as small as 1 cm^2^. The faster preparation allows for a readily available suspension compared to the cultured keratinocytes, where wait times can be a few weeks.

Few studies have comprehensively assessed the effectiveness of the RES™ in the management of childhood burn injuries. Most of the published literature is based on the adult cohort and there is a paucity of data based on the paediatric population. When compared to standard care, wounds treated with RES™ had longer operative times [29], more wound infection [10] and once applied the RES™ requires a retention dressing such as Biobrane®, to keep *in situ* [10]. However, in the other studies, application of RES™ was associated with less post-operative pain [10, 29], smaller donor site area [29, 30], shorter TTRE [10, 29, 30], fewer dressing changes and cost-effectiveness [10, 31]. Autologous skin cell suspensions show promising potential to change current burn wound management approaches from dressing based to cell-based therapy.

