First introduced in 1979 [11], Biobrane® (Smith and Nephew, Hull, UK) is a composite biosynthetic skin substitute composed a matrix of short porcine collagen peptides bonded to a layer of nylon that is enveloped in silicone [8]. The benefits of using Biobrane® include shorter TTRE, improved mobility, shorter hospital stay, ease of application, ability to visualise the wound [32] and reduced pain [10–12, 33, 34]. For clean wounds, this transparent dressing is able to stay *in situ* for up to 14 days, thus supporting the cost-effective treatment of burn injuries [35]. Failure of Biobrane® to adhere to the wound bed occurs once counts exceed 10^5^ organisms/gram of tissue [36]. Reported infection rates associated with Biobrane® range from 5 to 22% [12, 37, 38]. However, Lal. et al. demonstrated that infection rate upon application of Biobrane® to superficial partial thickness scald burns in children with 48 h of injury did not differ when compared to a topical silver dressing [39]. Biobrane® recreates the barrier function of the skin and has been used as a dermal salvage option for burn wounds over the last four decades.

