### Randomisation and allocation

To reduce the chance of prediction of treatment allocation, a procedure which randomly allocates participants in groups using a random step size will be used [77]. The randomisation sequence will then be uploaded into Research Electronic Data Capture (REDCap) randomisation module [78] by a third party person not associated with the study. Upon obtaining informed consent for the participation, baseline data (participant demographics including Fitzpatrick Skin Type, burn injury time, depth, TBSAB, injury mechanism and history of first aid prior to enrollment) will be collected. An investigator aligned with the study will complete the randomisation using REDCap and inform the treating clinicians of the allocated intervention group.

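### The adverse-event capture rule contradicts itself on relatedness, and wound infection, a named harm, is not an outcome compared by arm

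*Protocol article*

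**What the plan says.** **Scope of safety monitoring.** The Monitoring section begins from an expectation: "Minimal adverse events are expected from the proposed interventions". It names infection, haematoma and intensive care admission as known possible events. It then sets the scope: "Adverse events related to the interventions will be monitored through review of patient medical records", and also "by guardian and participant (where applicable) self-report and by the treating clinicians". The following sentence is wider: "All adverse events will be communicated to the clinical health service and Human Research Ethics Committee (HREC". The same section adds: "An independent Safety Monitoring Group will also monitor all aspects of patient safety throughout the study on a regular basis".

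**Who knows the arm.** Under Randomisation and allocation, an investigator randomises in REDCap and will "inform the treating clinicians of the allocated intervention group". Under Operative procedures, the attending burns surgeon or the registrar applies RES and Biobrane. The Blinding section nevertheless describes care providers as blinded. The masked assessments it sets out concern wound and scar images and scar thickness, not adverse events.

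**Infection.** The Background states: "Reported infection rates associated with Biobrane® range from 5 to 22" per cent. It then cites one study of superficial partial thickness scalds in children, treated within 48 h, in which infection with Biobrane was no different from infection with a topical silver dressing. For RES, it cites one study with more wound infection than standard care. The outcomes in the Abstract, Aims and Study outcomes are re-epithelialisation time, pain, itch, scar severity, quality of life, satisfaction, ease of application and resource use. Neither infection nor adverse events are among them. The Discussion says that limitations of infection diagnosis will be adjusted for in the analysis.

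**The concern.** A rule that admits an event only if it is thought related to the treatment makes a causal judgement the condition for entering the data. In an open-label comparison that judgement can depend on the arm. An infection under the site's routine silver dressing may be put down to the burn, and the same infection under Biobrane or RES to the product. The opposite lean is also possible. Either way, recorded counts could differ between arms when the true rates do not.

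Infection is where this matters most. It is the harm that the Background itself discusses for the two newer approaches, and the trial sets out to identify the most effective approach of the three. As the article stands, that conclusion could be drawn with no planned estimate of infection under each dressing.

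**Working it through.** No stated figure underlies this point, so the main check sets the sections side by side. The arithmetic only gives scale.

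1. **Scope.** The monitoring sentence covers related events. The communication sentence covers all events, and the Safety Monitoring Group's remit covers all aspects of safety. Events that are not monitored cannot be reliably communicated, so the first scope and the second cannot both be the working rule.

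2. **Knowledge of arm.** Three sources are named: medical records, self-report by guardian or participant, and treating clinicians. The clinicians are told the allocation, and the surgeon or registrar applies the RES and Biobrane. The statement that care providers are blinded is incompatible with both. The document does not say who decides relatedness and describes no masked assessment of adverse events.

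3. **Infection in the plan.** It is named in Monitoring, quantified in the Background, absent from every list of outcomes, and present in the analysis only through adjustment.

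4. **Expected counts.** Inputs: 28 children per group (Sample size estimate), hence 56 in groups B and C; rates of 5% and 22% (Background, for Biobrane). Assumption: these rates apply to both Biobrane-containing groups.
   - Groups B and C together: 56 × 0.05 = 2.8 and 56 × 0.22 = 12.3.
   - Per group: 28 × 0.05 = 1.4 and 28 × 0.22 = 6.2.

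5. **Effect of a relatedness filter.** If the true rate is *p* in both arms, and shares q₁ and q₂ of infections are called related, the recorded ratio is (p × q₁)/(p × q₂) = q₁/q₂. The document gives neither share. With assumed shares of 0.9 in one arm and 0.9, 0.7, 0.5 or 0.3 in the other, the ratio is 1.0, 1.3, 1.8 or 3.0. The range starts at no bias, and the document does not place the trial anywhere in it.

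6. **What a by-arm comparison could support.** Assume true rates of 5% and 22% in two arms, a two-sided 0.05 level and mean rate p̄ = (0.05 + 0.22)/2 = 0.135. Power is Φ{[|p₁ − p₂| − 1.96√(2p̄(1 − p̄)/n)] / √[(p₁(1 − p₁) + p₂(1 − p₂))/n]}.
   - n = 28: Φ[(0.170 − 1.96 × 0.0913)/0.0885] = Φ(−0.10) = 46%.
   - n = 25 (28 × 0.9 = 25.2 after 10% attrition): Φ[(0.170 − 1.96 × 0.0966)/0.0936] = Φ(−0.21) = 42%.
   - 80% power would need 63 per arm. The trial can estimate infection by arm but not test it with adequate power.

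**The case against.** The strongest reply is that the section, read whole, covers all events. The word *only* does not appear, the next sentence speaks of all adverse events, and an independent group watches every aspect of safety. Records and family reports supplement the clinicians, and under Post-operative care discharged families are told to report concerns, especially fever or erythema. The Background's most closely matched study found no infection difference between Biobrane and topical silver. Adjusting for infection diagnosis implies that diagnoses are recorded, so a by-arm table could be made. Adverse-event forms, causality rules and infection criteria are commonly left to a full protocol or analysis plan, and the data collection table is not reproduced in the text available.

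Much of this stands, and it rules out several inferences that a reader might draw:
- **That unrelated events are definitely discarded.** The text conflicts with itself. It does not settle on the narrow rule.
- **That clinicians who know the arm decide relatedness.** They are one reporting source, and no judge is named.
- **That the Safety Monitoring Group sees a filtered count.** Nothing says so, and its stated remit points the other way.
- **That the safety comparison is biased, or that a fair one is impossible.** Differential attribution is a risk under one reading, and infection data probably will exist.
- **That the Background contradicts the expectation of few adverse events.** It points both ways for Biobrane, and the RES signal comes from one cited study.

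The reply does not remove the wording conflict, which is stated text and not an omission due to condensation. Nor does it explain why outcome lists detailed enough to include ease of dressing application leave out the harm named first under Monitoring. The no-difference study concerned Biobrane on superficial partial thickness scalds, not RES or mid-dermal burns.

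**Conclusion.** The concern holds in a limited form. The capture rule is internally inconsistent. If the narrow wording is followed, entry depends on a relatedness judgement where a reporting source knows the arm, so ascertainment could differ between groups. The size and direction of any resulting bias cannot be derived from the document, and the ratios above depend wholly on assumed attribution shares. The statement that care providers are blinded contradicts two other sections.

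Separately, infection is acknowledged as a harm and earmarked for adjustment, but the article plans no comparison of it by arm. At the cited Biobrane rates, about 3 to 12 infections in groups B and C would go without a planned by-arm estimate. This warrants a correction to the protocol. It does not show that the trial's safety data are unusable.

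**What to change.** 1. **Monitoring.** Replace the sentence on scope with one saying that all adverse events are recorded in all three arms from randomisation to the 12-month review, with relatedness entered as an attribute of each event and not as a condition of entry.
2. **Study outcomes.** Add wound infection up to ≥ 95% re-epithelialisation as a secondary safety outcome. Use one criterion, chosen by the investigators and applied identically in the three arms. Report it by arm with 95% confidence intervals, described as an estimate and not a powered test.
3. **Blinding.** Reconcile the statement that care providers are blinded with Operative procedures and with Randomisation and allocation, so that the document says plainly who knows the arm.

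The cost is protocol wording and an adverse-event form in REDCap. The sources are already to be reviewed, and no extra participants are needed. The downside is that more unrelated events will have to be recorded.

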## Study outcomes

### Primary outcome: TTRE

Wound re-epithelialisation time is defined as the number of days from date of burn injury to ≥ 95% wound re-epithelialisation or date of skin graft as determined by the attending burns surgeon. Subjective assessment by an experienced burn surgeon is validated and reliable and will be the primary approach for TTRE [52, 53]. Objective assessment with three-dimensional (3D) digital camera imaging will be the secondary approach. Wound re-epithelialisaton will be expressed as a percentage using wound area (cm^2^) and perimeter (cm) calculated on the first dressing change day and the day a clinical assessment of ≥ 95% wound re-epithelialisation is made by the attending burns surgeon. The first dressing change is usually within 3 to 5 days after the burn injury. This allows for the burn wound to declare full extent and represent the maximal possible wound area in the absence of infection.

Images taken with the 3D LifeVizII System® (Quantificare S.A., Cedex, France) will be analysed using Dermapix® v3.0 (Quantificare S.A., Cedex, France). This fast, non-invasive 3D clinical imaging approach is ideal for children. The 3D LifeVizII System®/Dermapix® has been validated in the assessment of partial thickness burn injuries (intraclass correlation coefficient (ICC) 0.96, 95% confidence intervals (CI) 0.93–0.97) [54, 55]. However, the Dermapix® software is time-consuming as it requires the images to be first uploaded, then stitched and lastly, analysed. Hence, using Dermapix® does not provide a real-time analysis of the wound.

A second 3D camera, the Intel® RealSense™ Depth Camera D415 (Intel, CA, USA) with corresponding GPC 3D WoundCare (GPC, Swansea, UK) software will be used as a second secondary objective measure of TTRE. The reliability of the WoundCare Lite (ICC 0.985, 95% CI 0.905–0.996) [41] and instantaneous availability of analysed data output is advantageous over the 3D LifeVizII System®/Dermapix®. Validation in the paediatric burn wound population is currently in progress, as this technology is relatively new.

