## Background

Burns are the fifth most common cause of non-fatal injuries in children younger than 16 years [1]. Paediatric burn injuries are associated with the burden of both functional and psychological challenges to the child [2–4] as well as the considerable expense incurred to health service providers who manage the burn care [5]. In 2017, three-fourths of acute burns treated at the Queensland Children’s Hospital in Brisbane and approximately half of recorded burn cases across Australia and New Zealand [6] were partial thickness burn injuries. The available wound management options are not without inherent disadvantages including but not limited to delayed wound healing [7–12]. Thus, current practice is driven to facilitate faster wound re-epithelialisation to improve scar outcomes [13] and reduce healthcare costs [10, 14].

Partial thickness burn injuries have a varied time to re-epithelialisation. Superficial partial thickness burns ideally heal within 14 days without requiring surgical intervention. Typically, deep partial thickness wounds are anticipated to have a prolonged time to re-epithelialisation (TTRE), often requiring a skin graft. Mid-dermal thickness wounds can potentially re-epithelialise spontaneously, within 14 days and without surgical intervention [15]. However, this is not always the status quo and management of intermediate depth burns remains contentious. Some surgeons prefer early skin grafting, whereas others advocate for conservative non-surgical management.

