#### Primary

To evaluate the effectiveness of three wound management approaches (standard care silver dressings (Acticoat® and Mepitel® or Mepilex Ag®)) or an autologous skin cell suspension (ASCS, harvested with the RECELL® ACH device) with Biobrane® or Biobrane® alone, in reducing the re-epithelialisation time of superficial partial to mid-dermal thickness burn injuries in children.

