## Data management

### Sample size estimate

The sample size estimate conducted for this trial is based on the primary outcome of TTRE. Using the Power Analysis and Sample Size (PASS) software (version 11.0.7; PASS, NCSS, LLC), a two-sided logrank test procedure was used. A total sample size of 84 subjects (28 participants per group) that accounted for a 10% attrition rate would achieve 80% power at a significance level of 0.05 [10, 75, 76]. A clinically important difference of 4 days for re-epithelialisation was used for the sample size estimation.

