### Statistical analysis

In the exploratory stage, data will be graphed, and summary statistics will be calculated for all outcomes. Data will be analysed using the ‘Intention to Treat’ principle. The primary outcome data will use the survival analysis model (both Kaplan-Meier analysis and Cox proportional hazards regression), with the time to healing as the main outcome and dressing group as the explanatory variable. All other data will be analysed using appropriate methods for longitudinal data such as mixed model’s regression analysis or generalised estimating equations (GEE). A GEE is better suited for estimating population average effects whereas mixed models are better suited for understanding the source of correlation and its structure. Thus, they are complementary ways of analysing the data rather than opposing. It should also be noted that for symmetrical outcome variable distributions (such as normally distributed) both methods should give similar results. Statistical significance will be set at *p* < 0.05. The data set will be analysed with SPSS (IBM Corporation, Armonk, NY, USA) and Stata (StataCorp, College Station, TX, USA) software where appropriate.

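### The primary outcome ends at healing or at skin graft without telling them apart, so more frequent and early grafting in one arm would be scored as faster healing

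*Protocol article*

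**What the plan says.** Under Primary outcome: TTRE, the protocol article counts days from injury to at least 95% "wound re-epithelialisation or date of skin graft as determined by the attending burns surgeon". Either date closes the clock, and no distinction is drawn between them.

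The primary aim is to compare three approaches "in reducing the re-epithelialisation time of superficial partial to mid-dermal thickness burn injuries in children". The Statistical analysis section specifies Kaplan-Meier and Cox regression "with the time to healing as the main outcome and dressing group as the explanatory variable". It does not say how a graft is coded. The Sample size estimate rests on the same outcome: "a two-sided logrank test procedure was used", and the stated number "would achieve 80% power at a significance level of 0.05".

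The Background presents grafting as what follows slow healing. Deep partial thickness wounds are described as having a "prolonged time to re-epithelialisation (TTRE), often requiring a skin graft", and a lower need for grafting is listed among the advantages of one of the silver dressings. On burns of intermediate depth it notes: "Some surgeons prefer early skin grafting, whereas others advocate for conservative non-surgical management". Under Monitoring, "Discontinuation or alteration of treatment will be at the discretion of the treating clinical team".

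No section of the article treats a graft as failure, as a competing event, as a separate outcome, or as the subject of a sensitivity analysis.

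**The concern.** In a time-to-healing analysis, shorter is better. A graft date is not a healing date, and by the article's own account grafts go to wounds that are not closing by themselves. A definition that stops the clock at graft can therefore give the worst wounds short times. An arm in which the dressing fails more often, and is followed by early grafts, would gain events and a higher apparent healing rate. The primary comparison would then credit an unfavourable result as benefit, and the reported quantity would not be the re-epithelialisation time named in the aim.

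**Working it through.** **Inputs from the article.** 28 children per group (3 × 28 = 84), 10% attrition, two-sided log-rank test at 0.05, 80% power, a 4-day difference. Evaluable per arm: 28 × 0.9 = 25.2, taken as 25.

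**The plan's own figure.** The total of 84 can be neither reproduced nor refuted, because no control median or hazard ratio is given. As a yardstick, suppose all 50 children in a pairwise comparison reach the event. Schoenfeld's formula, events = 4(1.96 + 0.84)² / (ln HR)², set to 50 gives a detectable HR of about 2.21. The present point does not depend on this number.

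**Assumptions for the check (none is in the article).** Identical underlying healing in both arms, Weibull with median 14 days and shape 3. The slowest wounds in each arm are grafted on a fixed day.

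**By hand, 1 v 5 grafts of 25 (4% v 20%) at day 12.**
- Weibull scale = 14 / (ln 2)^(1/3) = 15.82 days.
- The slowest 20% would heal after 15.82 × (ln 5)^(1/3) = 18.5 days, yet are recorded at day 12.
- Healed spontaneously by day 12: 1 − exp[−(12/15.82)³] = 35% in each arm.
- With grafts scored as events, the Kaplan-Meier proportion at day 12 is 35 + 20 = 55% in the more-grafted arm and 35 + 4 = 39% in the other.
- Spontaneous healing is eventually reached by 80% and 96%. The ranking of the arms is reversed.

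**By simulation, log-rank test, 25 per arm, 800 runs per scenario.** HR above 1 favours the more-grafted arm. The nominal rate of falsely declaring that arm faster is 2.5%. Ranges are across repeated sets of runs.

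| Grafts, day | HR, graft as event | Falsely faster |
|---|---|---|
| 1 v 8, day 12 | 2.24–2.34 | 69–70% |
| 1 v 5, day 12 | 1.68–1.70 | 37–40% |
| 1 v 5, day 14 | 1.56 | 30–35% |
| 1 v 5, day 17 | 1.32 | 14–16% |
| 1 v 5, day 21 | 1.05 | about 5% |
| 1 v 3, day 12 | 1.32 | 18% |
| 1 v 2, day 12 | 1.17 | 9–12% |
| 1 v 5, day 12, slow wounds picked imperfectly | 1.35 | 19% |
| 3 v 3 | 0.99 | 6%, no systematic direction |

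For 1 v 5 at day 12, the spurious effect is ln 1.70 / ln 2.21 = 0.53 / 0.79, about two thirds on the log scale of the effect that 50 events can detect with 80% power.

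**Other codings, 1 v 5 at day 12.** Censoring at graft: falsely faster in 21–22%. Keeping grafted children as not healed: HR 0.78, falsely faster in 0%.

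**A different healing distribution** (lognormal, median 14 days, log-SD 0.35; 0 v 5 grafts at day 10; 1,500 runs): graft as event 61%, censored 31%, kept as not healed 0%. With graft as event, for 2, 5 and 8 grafts of 25 in one arm and none in the other, the figures are 20%, 64% and 94% at day 8; 16%, 42% and 63% at day 14; and 5%, 3% and 1% at day 21.

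**The case against.** The analysis section never says that a graft is coded as an event, and coding rules are commonly left to an analysis plan that is not shown here. This is fair: event coding is the natural reading of the definition, not an explicit statement. It does not rescue the endpoint, because censoring at graft still favours the arm with more early grafts.

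The size also depends on favourable choices. The article gives no graft rate or day. It excludes deep dermal and full thickness wounds, and it is deep partial thickness wounds that it describes as often needing grafts. The large figures need grafting that is both unequal and early; late, rare or equal grafting leaves little or no directional bias. This stands too, and limits what can be claimed about size. Mid-dermal wounds remain eligible, however, and grafting was expected often enough to be written into the primary outcome.

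A reader might infer that surgeons at this site graft early and, knowing the allocation, do so differently by arm. The article does not support that. The Background sentence on early grafting describes a general debate, not local practice. On allocation the article conflicts with itself: Randomisation and allocation has the treating clinicians told the group, while Blinding says care providers do not know it. Those two sections must be reconciled, but the point here needs neither inference.

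Finally, the composite could be kept and renamed as time to wound closure, with graft rates and spontaneous healing reported beside it. That would remove the mislabelling, but the primary comparison would still improve when grafts are done early.

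**Conclusion.** The point holds as a flaw in the stated definition: the primary outcome merges healing with a marker of failed healing, while the aim and the analysis speak of healing alone. Confidence in this is high.

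The consequence is conditional. If one arm has more grafts and they come before or around the usual healing time, that arm is scored as healing faster. Under the Weibull assumptions, the false-faster rate runs from about 5% (1 v 5 at day 21) through 9–12% (1 v 2 at day 12) and about 40% (1 v 5 at day 12) to 69–70% (1 v 8 at day 12). Confidence in any one of these figures is moderate at most.

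It is tempting to say without qualification that the endpoint reverses the trial's answer. The article does not support that, because it gives neither the frequency nor the timing of grafts, and equal grafting produces no systematic direction.

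**What to change.** In the outcome definition, make the primary event spontaneous re-epithelialisation of at least 95%. In the analysis section, treat skin grafting as a competing event. Compare the cumulative incidence of spontaneous healing between arms, with grafted children kept in the risk set as not healed (for example a Fine-Gray model), and state that they are not censored at graft. Report the number and proportion grafted by arm. Keep the present outcome as a sensitivity analysis, named as the composite of healing or graft.

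The cost is about two sentences. No new data are needed, because the current definition already requires the graft date. The drawback is slightly fewer primary events if grafts occur. The change concerns only how grafts are counted; no change to any clinical decision about grafting is proposed.
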